#### Blinding

The therapists will be aware of the treatments in both groups as they are experienced enough to distinguish between the treatment methods; however, the participants will remain blinded to the treatment. Participants will be told that they have been randomly allocated to either the treatment group or the control group, and they will be treated with bloodletting using a three-edged needle, regular acupuncture, or both, based upon their condition. Moreover, the study will utilize independent data managers and statisticians who will also remained blinded to the intervention methods throughout the trial. All therapists, data managers, and statisticians have been requested to refrain from communication with each other regarding the study.

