#### Treatment group

Acupuncture utilizing the waking up the spirit needling method will be performed as follows. First, patients will adopt a supine position, then the operators will sterilize the skin of an area of 3 cm around acupoints with 75% alcohol. Acupuncture bloodletting will be conducted at acupoints *Bai Hui* (DU-20), *Si Shen Cong* (EX-HN1), and at 12 well-points using a three-edged needle which will be inserted into the skin at a depth of approximately 5–10 mm. The needle will be withdrawn immediately, and the skin around the pin hole will be squeezed to release a few drops of blood. The 12 well-points are *Shao Shang* (LU-11), *Shang Yang* (LI-1), *Li Dui* (ST-45), *Yin Bai* (SP-1), *Shao Chong* (HT-9), *Shao Ze* (SI-1), *Zhi Yin* (BL-67), *Yong Quan* (KI-1), *Zhong Chong* (PC-9), *Guan Chong* (SJ-1), *Zu Qiao Yin* (GB-44), and *Da Dun* (LR-1). Lastly, other points, such as *Ren Zhong* (GV-26), *Cheng Jiang* (CV-24), *Feng Chi* (GB-20), *He Gu* (LI-4), *Lao Gong* (PC-8), *Tai Chong* (LV-3), and *Yong Quan* (K-I1), will be chosen after the bloodletting, and the filiform needles will be inserted to depth of 10–15 mm and manually manipulated by rotation in order to produce a characteristic sensation known as “*De Qi*.” Techniques of mild reinforcing and attenuating will be applied, and the filiform needles will be retained for 30 min.

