#### Adverse events

Adverse events (AEs) are defined as negative or unintended clinical manifestations following the treatment [57]. Our investigators will collect information regarding AEs every 3 days. Participants will be instructed to report any abnormal reactions or uncomfortable feelings experienced to any researcher. All related and unexpected AEs will be recorded on Case Report Forms (CRFs) in detail, including time of occurrence, degree of AE, and possible causes. Patients with mild and moderate AEs will be treated for their symptoms and closely monitored as necessary by the researcher. Severe AEs will be reported to the Research Ethics Committee, which will provide medical advice to the research team within 48 h, and the Research Ethics Committee will determine whether the patient is eligible for further treatment associated with the study.

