## Discussion

This trial aims to investigate whether acupuncture utilizing the waking up the spirit needling method can improve CVR capacity in patients with acute cerebral infarction, thus reducing NIHSS scores and preventing further disease progression. Some studies [60–62] have demonstrated that acupuncture may improve symptoms in patients with cerebral infarction and, according to clinical observations, acupuncture utilizing the waking up the spirit needling method may produce similar effects. Furthermore, increased focus has been directed at the relationship between CVR and cerebral infarction [32]. Acupuncture is widely utilized in the treatment of cerebral infarction, though the mechanisms underlying its effects remain unclear. In this randomized, controlled study we expect that participants will experience pain relief as well as improved function and strength. Furthermore, data and evidence gained from this study will be utilized in the development of future research projects regarding the effects of acupuncture in patients with acute cerebral infarction.

The risks of taking part in this trial are minimal. Acupuncture is a very safe treatment when conducted by properly trained clinicians. Occasionally, acupuncture can make people feel nauseous, faint, or experience a temporary increase in pain either during or after treatment.

The global outlook for cerebral infarction is not good [4, 63], and both first- and second-level prevention are critical at reducing the impact of this potentially life-threatening and devastating condition [63–70]. CVR is an independent risk factor for the occurrence [18–21], progression [22–25], and recurrence [26] of cerebral infarction that requires attention. Some researchers have even proposed that CVR should be assessed regularly, as one of the key targets for prevention [71].

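### The adverse-event recording rule is narrower than the definition and collection rule beside it, so the CRF safety record may be incomplete and possibly unequal between arms

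*Protocol article*

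**What the plan says.** The Adverse events section of the protocol article has four relevant sentences.

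- Definition: "Adverse events (AEs) are defined as negative or unintended clinical manifestations following the treatment". Neither cause nor expectedness is a condition.
- Collection: "Our investigators will collect information regarding AEs every 3 days", and "Participants will be instructed to report any abnormal reactions or uncomfortable feelings experienced to any researcher". Again there is no filter.
- Recording: "All related and unexpected AEs will be recorded on Case Report Forms (CRFs) in detail". The sentence goes on to list timing, degree and possible causes as the details to be entered.
- Escalation: "Severe AEs will be reported to the Research Ethics Committee", with no relatedness or expectedness condition.

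Table 1 ticks adverse events in every column, from baseline to follow-up. The Discussion names reactions that the investigators already foresee: "Occasionally, acupuncture can make people feel nauseous, faint, or experience a temporary increase in pain either during or after treatment". Under Treatment group, "Acupuncture bloodletting will be conducted at acupoints" on the head and at the 12 well-points; the Control group section names filiform needles only. On blinding, the article says "The therapists will be aware of the treatments in both groups".

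**The concern.** Relatedness and expectedness are properties of an event that a safety record should hold. The recording sentence appears to use them as conditions of entry. An event can then meet the definition, be found at a 3-day check or reported by the patient, and still not be required on the CRF.

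Two things make this more than a matter of wording. First, foreseeable reactions are the ones a filter on unexpectedness would remove, and one arm has a procedure (skin puncture with a three-edged needle, then squeezing for blood) that the other arm's description lacks. Second, relatedness is a judgement, and the therapists know the allocation. This is a pilot whose data are meant to inform later research, so a filtered record would hand the next trial a weaker account of tolerability.

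**Working it through.** No arithmetic applies: the article attaches no AE rate or power figure to this rule. The check is to sort events by the two attributes and see which combinations each reading of the sentence requires on the CRF.

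| Event judged | Meets the definition | Collected | Recorded, reading A (both conditions) | Recorded, reading B (all related plus all unexpected) |
|---|---|---|---|---|
| Related, unexpected | yes | yes | yes | yes |
| Related, expected | yes | yes | not required | yes |
| Unrelated, unexpected | yes | yes | not required | yes |
| Unrelated, expected | yes | yes | not required | not required |

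Reading A, the plain one, requires one of the four combinations; reading B requires three. These are counts of categories, not shares of events.

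**Reading A.** Nausea, faintness and a temporary rise in pain are foreseen in the Discussion, so they are expected and fall in the second row. Local effects of bloodletting fall there too if they are classed as expected. The article does not class them, so that step is an assumption, though a natural one for a procedure meant to draw blood.

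**Reading B.** Related harms of either needling method are kept. The last row is still lost. Worsening of an acute infarct could sit there if someone judges it expected and unrelated to treatment.

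**Do other sections restore the record?**

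- Data management says that all participant data go on the CRFs at the end of the treatment period. This is a general statement. The measurements that section lists are CVR, BHI, NIHSS and Barthel Index, not AEs.
- Reporting of severe AEs to the ethics committee covers neither mild nor moderate events, and a report to a committee is not a CRF entry.
- NIHSS at weeks 1 and 2, disease exacerbation as a discontinuation reason, and recurrence at 3 and 6 months all pick up stroke worsening. They do not necessarily log it as an AE with onset and cause, and they do not cover other kinds of event.
- Table 1 schedules AEs in every period but does not say which are recorded.

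None of these requires a CRF record of a mild or moderate event that the recording sentence leaves out.

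**Who applies the filter.** Investigators collect AEs; therapists are unblinded. The article does not say who decides relatedness or whether that person knows the allocation.

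**The case against.** The best defence is that the sentence never says that other events are excluded. It promises to record one class in full and may govern only the level of detail. The setting is inclusive: patients report anything abnormal, checks are regular, and possible causes are themselves a CRF item, which fits poorly with cause being settled before entry. This stands as far as it goes. The exclusion is an inference from the wording, and the text is ambiguous. But an ambiguous entry rule can be applied differently by different staff, and none of its readings promises the same detail for every event that meets the definition.

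Three stronger conclusions may tempt a reader, and the documents do not support them.

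- *That bloodletting harms will go unrecorded.* This depends on reading A and on classing those harms as expected. The reactions named in the Discussion are described for acupuncture in general, and both arms receive acupuncture. Unequal loss is plausible, not shown.
- *That stroke worsening judged unrelated disappears.* It is partly captured by NIHSS, discontinuation reasons, severe-AE reporting and recurrence follow-up.
- *That a planned safety comparison between arms is biased.* The Statistical analysis section states no such comparison. One may exist in a plan not shown, and its absence here is not a fault. What is affected is the safety record.

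Nor can bias be read from the blinding section alone: it describes the therapists, not whoever judges relatedness.

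**Conclusion.** The point holds in limited form. Within one section the recording rule is narrower than the definition and the collection rule, and this is true on both readings A and B. Only the extent differs: reading A leaves out three of the four combinations of relatedness and expectedness, reading B leaves out one. The consequence is a CRF safety record that could be incomplete, that depends on a causality judgement by an unnamed person of unstated blinding, and that could be unequal between arms because bloodletting is described for one arm only.

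The size in events cannot be given, since the documents offer no rates. The conclusion assumes that staff follow the sentence as written and that the general statement in Data management does not override it. If the sentence was meant only to set the level of detail, the remaining problem is one of unclear wording and uneven detail, and the same correction settles it.

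**What to change.** Reconcile the recording sentence with the definition and Table 1. Suggested wording: *All adverse events, whether or not considered related to treatment or expected, will be recorded on the CRF over the periods shown in Table 1, with onset, severity, relatedness and expectedness as recorded fields, and will be summarised by arm.* It would help to state in the same place who assesses relatedness and whether that person knows the allocation.

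The cost is one protocol sentence, a few CRF fields and slightly more data entry for 60 patients. The Trial status section says that no interventions had been applied at manuscript submission, so at that point the change would have touched no collected treatment-period data.

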### Data management

All researchers including therapists, data entry clerks, the data collector, data manager, statistician, and outcome assessors will receive special training regarding the research contents and data management. During the recruitment period, our data collector will record the baseline characteristics of participants on CRFs, and all data will be assessed by the data manager. Then, as the study begins, the data collector will obtain CVR, BHI, NIHSS, and Barthel Index data at baseline and 2 weeks following the first treatment. Additional NIHSS and Barthel Index data will be obtained 1 week following the first treatment. The TCD assessment will be conducted by an appointed operator who has completed an advanced course of study in this field at Beijing Tiantan Hospital Affiliated with Capital Medical University.

Upon conclusion of the treatment period, all participant data will be completed and recorded on the original CRFs. The data will then be entered into Excel spreadsheets by two separate data entry clerks, following which the data manager will compare the accuracy of the two datasets. If any differences are noted, corrections will be made according to, and marked on, the original CRFs. The data will be managed in accordance with the Data Protection Act of 1998 [58]. All paper files related to the research will be saved in a locked filing cabinet, while electronic documents will be stored in a special computer which will remain password-protected and accessible only to the principal investigators. All research documents, including both the paper files and electronic documents, will be preserved for at least 5 years after publication. If readers have any questions regarding our published data, they will be permitted to contact our first author or corresponding author to ask for the original data.

### Statistical analysis

Data analysis will be performed by statisticians who are blinded to the entire allocation and intervention process. The statisticians are affiliated with the Research Center of Clinical Epidemiology at Peking University Third Hospital in Beijing, China, which is one of the most authoritative statistics centers in the country. An intention-to-treat analysis will be conducted using the SPSS statistical software package (V.22.0) (International Business Machines Corporation). Two-tailed analyses will be conducted, with the level of statistical significance defined as *P* < 0.05. Baseline characteristics, such as gender, age, NIHSS score, GCS score, previous duration, and impaired CVR, will be analyzed. The categorical data will be described as *n* (%), and continuous data using mean ± SD. If the data meets the standard of the parameter test, a chi-square test will then be conducted. Independent sample *t* tests will be used for comparisons among the groups, while paired *t* tests will be used for within-group comparisons. The efficacy of the intervention will be compared between the two groups using *χ*
^2^ analysis.

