## Methods

### Objectives

The present study aims to test the hypothesis that acupuncture utilizing the waking up the spirit needling method can improve CVR capacity in patients with acute cerebral infarction, thus reducing NIHSS scores and preventing further disease progression.

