### Participants

#### Sample size

As we were unable to find any publication regarding acupuncture for CVR capacity, we could not calculate the appropriate sample size according to the sample size calculation formula. We determined an appropriate sample size of 60 for a pilot study. Both the treatment and control groups will contain 30 eligible participants. The outcomes of this study will aid in the calculation of the appropriate sample size for further randomized clinical trials.

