#### Inclusion criteria

Patients of either sex are eligible for entry into this study if they meet the following inclusion criteria: (1) age between 30 and 80 years with acute cerebral infarction, with an onset time of less than 7 days, (2) confirmed as meeting the Western medicine diagnostic criteria for cerebral infarction issued by the American Heart Association/American Stroke Association (AHA/ASA) in 2015 [52], (3) confirmed as meeting the traditional Chinese medicine diagnostic criteria developed by the Stroke Diagnosis and Curative Effect Evaluation Standard (Draft) of the State Administration of Traditional Chinese Medicine, Acute Encephalopathy Research Group [53], (4) confirmation of diagnosis by head CT or MRI, (5) confirmed CVR impairment as assessed using the breath-holding-test, (6) NIHSS score within the range of 5–20 points, (7) Glasgow Coma Scale score ≥12 points, and (8) agreement to participate in this trial and signing an signed Informed Consent Form.

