Acupuncture provides distinct advantages in that it is easy, convenient, economic, and effective. The waking up the spirit needling method and the hand and foot 12-meridian needle method are commonly used in China for the treatment of stroke patients. Both of them have shown curative effect in clinical practice. It is noted, however, that the waking up the spirit needling method using bloodletting with a three-edged needle, provides stronger stimuli to the head than the hand and foot 12-meridian needle method. Since those bloodletting acupoints are located on the head, it is reasonable to hypothesize that this method might exert an impact on cerebral blood flow. The same effect is unlikely to be obtained by the hand and foot 12-meridian needle method which takes acupoints from the extremities. Significant differences in blood flow have been observed between strong stimulation and regular acupuncture, though the mechanism underlying these differences remain unclear [38–41]. Butylphthalide [45] has an effect on patients with acute cerebral infarction, the underlying mechanism maybe that it changes the CVR by changing blood flow. As with butylphthalide, we hypothesize that acupuncture utilizing the waking up the spirit needling method can improve CVR capacity in patients with acute cerebral infarction.

We chose the hand and foot 12-meridian needle method as the control intervention. The 12 acupoints stimulated in this method are located on the arms and legs, and the stimulation provided by this technique is considered to be less than that of bloodletting utilizing a three-edged needle. Therefore, the procedure should have less effect on CVR and cerebral blood flow. The 12-acupoint method is also taught by masters of acupuncture and is quite popular in clinical treatment. Furthermore, research has indicated that it is effective in improving patients’ symptoms [72]. Therefore, it is a reasonable control intervention that meets ethical standards.

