To our knowledge, the present trial marks the first attempt to investigate the efficacy of acupuncture with regard to improving CVR. The results of this trial may help to elucidate the mechanism underlying the effects of acupuncture in patients with acute stroke, which may significantly aid in the development of clinical treatment protocols and further studies regarding the underlying mechanisms of these effects. As research has indicated that adequate CVR is crucial for preventing the occurrence, progression, and recurrence of cerebral infarction, the results of this trial may also highlight the importance of regular assessment of CVR.

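### Unlabelled within-group paired t tests, in patients entered on a low CVR soon after stroke, cannot show a treatment effect; with two active arms the claim must be one method relative to the other

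*Protocol article*

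**What the plan says.** All references are to the protocol article.

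- **Entry.** Inclusion criteria require "confirmed CVR impairment as assessed using the breath-holding-test", with onset less than 7 days earlier. The outcome section defines impairment as a calculated CVR below 20% and uses the same test for both primary outcomes, CVR and BHI, at baseline and 2 weeks.
- **Background care.** The Follow-up section keeps every participant on conventional stroke therapy.
- **Analysis.** Statistical analysis plans independent-sample t tests between groups and a between-group chi-square test of efficacy, and adds that paired t "tests will be used for within-group comparisons". One rule covers all of these: "Two-tailed analyses will be conducted", and a P value below 0.05 counts as significant.
- **Size.** "Both the treatment and control groups will contain 30 eligible participants".
- **Objective.** The stated hypothesis reads: "acupuncture utilizing the waking up the spirit needling method can improve CVR capacity in patients with acute cerebral infarction, thus reducing NIHSS scores". Prevention of later worsening is added to it.
- **Comparator.** The Discussion says of the two needling methods: "Both of them have shown curative effect in clinical practice". It expects the 12-meridian method to have less effect on CVR.
- **Wider statement.** The Discussion also says that "the present trial marks the first attempt to investigate the efficacy of acupuncture with regard to improving CVR".
- **Baseline.** Table 1 lists CVR once as a pre-treatment entry item and again at Week 0 as a primary outcome. The outcome section speaks only of baseline.

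**The concern.** A paired t test within an arm asks whether the mean changed, not why. Here there are up to three reasons for change besides the needling: recovery in the first weeks after stroke, conventional therapy, and regression to the mean because patients were chosen for a low value of the outcome. All three operate in both arms, so randomisation removes them from the between-group difference but not from the within-arm change.

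Two misleading reports become easy. One is that CVR improved significantly with acupuncture. The other is that it improved significantly in one arm and not in the other, read as a difference between the methods. The design adds to the pull. With no sham or no-acupuncture arm, a statement about the efficacy of acupuncture on CVR has no randomised contrast behind it and could rest only on within-arm change.

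**Working it through.** There is no stated calculation to reproduce: the Sample size section sets 60 patients without a formula, and no CVR mean, SD or reliability is given.

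**Inputs from the protocol:** n = 30 per arm, two-sided 0.05, entry at CVR < 20%.

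**Assumed inputs:** population mean 15% to 25%, SD 10 to 12 points, test-retest correlation r 0.5 to 0.8, normal values. No treatment effect and no recovery.

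**Step 1: regression to the mean, qualifying value used as baseline.** With c = (20 − mean)/SD and λ = φ(c)/Φ(c):

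- mean of those selected = mean − SD × λ
- expected rise at 2 weeks = (1 − r) × SD × λ

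For mean 25, SD 12, r = 0.6: c = −5/12 = −0.417 and λ = 1.081. The selected mean is 25 − 12 × 1.081 = 12.0, and the expected rise is 0.4 × 12 × 1.081 = 5.2 points.

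**Step 2: chance of a significant rise.** In simulation the SD of change for that case is 9.9 points, so its standard error is 9.9/√30 = 1.81 and the expected t is about 5.2/1.81 = 2.9, against a critical value of 2.05. The paired test is significant upwards in 79% of arms. With p the chance in one arm and the arms independent, both are significant with chance p², and exactly one with chance 2p(1 − p).

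| Mean, SD, r | Expected rise (points) | A given arm | Both arms | Exactly one arm |
|---|---|---|---|---|
| 25, 12, 0.5 | 6.5 | 89% | 79% | 20% |
| 25, 12, 0.6 | 5.2 | 79% | 62% | 33% |
| 25, 12, 0.8 | 2.6 | 46% | 21% | 50% |
| 20, 10, 0.8 | 1.6 | 28% | 8% | 40% |
| 15, 10, 0.8 | 1.0 | 14% | 2% | 24% |

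The nominal rate of false improvement is 2.5% per arm. In the same null trials the two-sample t test on change rejects about 5% of the time. A wider grid (mean 10% to 30%, SD 10 to 15, r 0.5 to 0.95) gives 3.9% to 99.7% per arm.

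BHI is affected in the same way. By the protocol's formulas it equals CVR in per cent divided by breath-holding time, so selecting on CVR selects on BHI.

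**Step 3: a separate Week 0 value as baseline.** If CVR is measured again before the first session and that value is the baseline, the false rate falls to about 2.5% per arm. The selection effect is gone.

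**Step 4: recovery alone.** Let both arms improve equally, without selection, by an assumed standardised paired change d. The noncentrality is d√30:

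| d | A given arm | Both arms |
|---|---|---|
| 0.2 | 18% | 3% |
| 0.5 | 75% | 57% |
| 0.8 | 99% | 98% |

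Choosing the baseline well does nothing about this part.

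**Step 5: claims against the design.**

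- Waking up the spirit method better than the 12-meridian method on CVR: estimable from the planned between-group tests.
- Lower NIHSS with one method than with the other: also estimable, since NIHSS is a secondary outcome.
- Acupuncture as such improves CVR: not estimable, since both arms receive acupuncture.
- Lower NIHSS and less progression because CVR improved: no analysis of that link is described, and recurrence at 3 and 6 months is kept out of the assessment of the main outcomes.

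**The case against.** The best reply is that the protocol never rests its conclusion on the paired tests. The Statistical analysis section assigns efficacy to a comparison between the two groups, and the Discussion explains why the comparator should do less for CVR, so the randomised contrast is the intended test. The work is a pilot, much of the mechanism language is framed as hypothesis, and a full analysis plan may label the paired tests.

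Much of this stands, and it rules out stronger readings that a reader might infer:

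- *That both arms will show improvement without any effect.* Step 2 gives 2% to 79% for both arms, under inputs the documents do not supply.
- *That regression to the mean is certain to be present.* Table 1 lists CVR separately at Week 0, and the Data management section describes outcome data as obtained when the study begins, after the recruitment records. If that Week 0 value is the baseline, this part vanishes.
- *That paired tests are the only route to the stated objective.* The objective concerns the waking up the spirit method, and between-group tests for it are planned. Only the wider sentence on the efficacy of acupuncture lacks a randomised contrast.
- *That nothing analyses NIHSS.* It is compared between groups; what goes untested is the causal path through CVR.
- *That significance will be compared across arms.* No section plans this; the tests merely make it possible.

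The active comparator is a justified choice, not an error. What the reply does not answer is that significance tests of within-arm change stand beside the between-group tests, at the same threshold and with no stated limit on their use, while recovery and background care affect them whichever baseline is used.

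**Conclusion.** The point holds in a limited form. Within-arm significance in this trial cannot be evidence of a treatment effect, and the text neither says so nor states which CVR measurement is the baseline. If the qualifying value is used, false improvement occurs in about 14% to 89% of arms, and exactly one arm is significant in about 20% to 50% of null trials. These figures rest on the assumed mean, SD and correlation; the direction does not. With a separate Week 0 baseline the selection part goes and recovery remains: 75% per arm if the common standardised change were 0.5, again an assumption.

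The between-group analysis is sound in principle and can support a relative benefit. It is also modest in power: by the normal approximation, 30 per arm gives 80% power for a difference of (1.96 + 0.84) × √(2/30) = 0.72 SD. That makes it more tempting to lean on within-arm results if the comparison is inconclusive. This should be corrected, but it does not invalidate the trial.

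**What to change.** 1. Report within-arm means and changes descriptively, with no significance tests offered as evidence of efficacy.
2. Base every efficacy statement on the between-group difference at 2 weeks adjusted for baseline: ANCOVA with baseline CVR, BHI or NIHSS as the covariate for the respective outcome.
3. State which CVR measurement is the analysis baseline. If the Week 0 value in Table 1 is taken before the first session, name that one and not the qualifying value.
4. Word the objective and conclusion as waking up the spirit acupuncture with bloodletting compared with 12-meridian acupuncture, both added to conventional therapy. Leave the chain from CVR to NIHSS and progression as a hypothesis for a later trial, and bring the Discussion sentence on the efficacy of acupuncture into line.

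The cost is wording only. The covariates are already collected, no patients are added, and no visit is added. The Trial status section says that no intervention had been applied at submission. The downside is a more modest stated objective.
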